### Exclusion criteria

The exclusion criteria are as follows: (1) severe primary or malignant disease of the heart, brain, liver, kidney, or other organs or systemic disease at an acute or progressive stage; (2) surgery within 2 months accompanied by surgical site infection; (3) patients who have been hospitalized less than 72 h or who die within 72 h of hospitalization; (4) psychiatric patients and pregnant women; (5) active tuberculosis; (6) a history of allergy to on-treatment drugs; (7) recent drug and alcohol abuse; (8) patients who receive no other antibiotics or fail to respond to other antibiotics within 3 months prior to the clinical trial.

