### Randomization and allocation

In each study site, patients with MDRO HAP that fulfill the inclusion criteria and do not meet any of the exclusion criteria are assigned to the trial group or control group according to the corresponding random numbers extracted in the order at visit. Each study site will enroll 40 patients for a total of 200 over the five study sites. A random number table generated using Statistical Analysis Software (SAS), version 9.2, using the randomization method, will be used to assign the participants in a ratio of 1:1, with 100 patients each in the trial group and control group. A researcher will generate the allocation sequence and enroll participants and the clinical researchers will assign participants to interventions. The clinical researchers at each center will provide packaged drugs to the participants according to the randomization number on the packaging; the code labeling will conform to the principles of GCP. The statistician will uncover the blinding as necessary.

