### Interventions

The treatment course is 28 days.

The control group will be given standard Western medicine therapy, including: routine monitoring of vital signs; blood, arterial blood gas, and biochemical analysis; coagulation monitoring; step-down antimicrobial therapy; handle the respiratory secretions; mechanical ventilation; liquid nutrient support; maintenance of blood sugar, acid base, and electrolyte balance; correct coagulation function; etc.

The trial group will receive standard Western medicine therapy plus *Buzhong Yiqi* decoction (*Radix Astragali seu Hedysari* 45 g, *Radix Codonopsis* 15 g, fried *Rhizoma Atractylodis Macrocephalae* 15 g, prepared *Radix Glycyrrhiza* 15 g, *Radix Angelicae Sinensis* 10 g, *Pericarpium Citri Reticulatae* 9 g, *Rhizoma Cimicifugae* 12 g, and *Radix Bupleuri* 20 g; NONG’s granular preparation, dissolved in 200 mL warm boiled water and taken orally or by nasal feed once daily).

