### Secondary outcomes

Clinical pulmonary infection score (CPIS): CPIS is a comprehensive clinical and imaging standard to assess the severity of pulmonary infection. It includes the following indicators: body temperature, white blood cell count, tracheal secretions, oxygenation, X-ray pulmonary infiltration, and progress in etiology. The clinical pulmonary infection score is compared before and after treatment. The CPIS details can be found in Additional file 3. Evaluation of disease severity: the scores of patients in the two groups are compared using the APECHA II scoring system before and after treatment. Improvement rate in APECHA II score = (Post-treatment score − Pre-treatment score)/Pre-treatment score. The APECHAII details can be found in Additional file 2. Clearance of drug-resistant pathogens: observed on days 7, 14, 21, and 28.Comparison of mechanical ventilation time and success rate of weaning off the ventilator are calculated if appropriate.Comparison of mortality: mortality is compared on day 28 between the groups.Radiography indicators: pulmonary CT imaging results are compared between the groups before and after treatment.Number of hospitalization days: survival days of patients who die and hospitalization days of those who survive and are discharged.

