### Sample size

Considering that no previous studies have been conducted to calculate the sample size, and assuming that the withdrawal rate is less than 15% [23], we expect that 100 patients will be enrolled in each arm, and that the final sample size of each arm will be at least 85. The data we collect will be helpful to calculate the appropriate sample size in the future and provide reference for further large-scale research.

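### Hospital days has no value for survivors still in hospital when observation ends, so if that is day 28 the longest stays drop out and a true difference shrinks

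*Protocol article*

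**What the plan says.** Under Secondary outcomes, the protocol article defines hospital days as "Number of hospitalization days: survival days of patients who die and hospitalization days of those who survive and are discharged". This gives two classes: patients who die, and survivors who have left hospital. It names no starting point and no closing date for the count.

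The same section lists ventilation only by name: "Comparison of mechanical ventilation time and success rate of weaning off the ventilator are calculated if appropriate".

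Three other statements set the time frame:
- Interventions: "The treatment course is 28 days".
- Secondary outcomes: "mortality is compared on day 28 between the groups"; pathogen clearance is likewise last observed on day 28.
- Exclusion criteria: the trial leaves out "patients who have been hospitalized less than 72 h or who die within 72 h of hospitalization", so every participant has spent at least 72 h in hospital before entry, with no upper limit.

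Under Design and Participants, selection ends on May 31, 2021 and the study on June 30, 2021. Data analysis plans a t-test or a non-parametric test for measurement data and names no method for censored durations.

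**The concern.** The article does not leave this definition to another document. It states a rule, and the rule omits a kind of patient that is likely to occur. Participants are emergency and ICU patients with multi-drug-resistant hospital-acquired pneumonia, and some may well still be inpatients 28 days after entry.

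If those patients get no value, two things follow. The comparison loses the longest stays, which is where a treatment that shortens stay would show much of its effect. And the patients compared are no longer the randomised groups but those who died or left in time, a selection that treatment itself may change. If one arm truly leaves sooner, more patients are removed from the slower arm, and the two arms look more alike than they are.

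**Working it through.** **The plan's own figure.** Sample size states "we expect that 100 patients will be enrolled in each arm, and that the final sample size of each arm will be at least 85". Check: 100 × (1 − 0.15) = 85. It reproduces. The article gives no power, effect or standard deviation (SD) for any duration, so every input below other than 85 per arm and day 28 is an assumption.

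**Step 1: who gets a value if observation ends at day 28.**
- Died: yes (survival days).
- Survived and discharged by day 28: yes (hospitalization days).
- Survived and still in hospital at day 28: none.

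**Step 2: loss of the longest stays, exponential model.** Assume no deaths and stays after randomisation with mean m = 28 days in one arm and 20 in the other. Let q = exp(−28/m) be the share still in hospital at day 28.
- q: exp(−1) = 0.368 and exp(−1.4) = 0.247, so 37% and 25% are dropped.
- Mean among those discharged by day 28, m − 28q/(1 − q): 28 − 28 × 0.368/0.632 = 11.70; 20 − 28 × 0.247/0.753 = 10.84. Difference 0.9 days.
- Mean with everyone kept and stays capped at 28, m(1 − q): 28 × 0.632 = 17.70; 20 × 0.753 = 15.07. Difference 2.6 days.

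The comparison to make is 0.9 against 2.6 days, because the remedy also stops at day 28. The uncapped 8-day difference is not recoverable under either rule.

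**Step 3: another shape.** Take a gamma distribution with shape 2, the same means, and scale s = m/2 (14 and 10). With x = 28/s (2 and 2.8), the share still in hospital is e^(−x)(1 + x) = 0.406 and 0.231. The capped mean is 2s − s·e^(−x)(2 + x) = 20.42 and 17.08, a difference of 3.3 days. The mean among those discharged is (capped mean − 28 × share)/(1 − share) = 15.24 and 13.80, a difference of 1.4 days.

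**Step 4: effect on power.** Simulation with 85 per arm, 2,000 runs, no deaths, lognormal stays (log-SD 0.6), true ratio of stays 0.75, Mann-Whitney test at 0.05:

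| Control median stay (days) | Power, kept at 28 days | Power, dropped |
|---|---|---|
| 14 | 86% | 71% |
| 18 | 86% | 60% |
| 22 | 84% | 46% |
| 26 | 83% | 34% |

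With a control median of 18 days, dropping removes 23% of controls and 11% of trial patients, and the mean difference falls from 3.5 to 2.3 days. The direction was the same in every scenario; the size was not.

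**Step 5: time origin, if days were counted from admission.** Assume a post-randomisation SD of 10 days, an independent pre-randomisation SD s, and a true difference of 4 days. Total SD = √(100 + s²), standard error = SD × √(2/85), power = Φ(4/SE − 1.96).
- s = 0: SE 1.53, power 74%.
- s = 5, 10, 15: SE 1.71, 2.17, 2.77; power 65%, 45%, 30%.

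Randomisation balances pre-entry time on average, so this loss is one of precision.

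**Step 6: why the remedy needs a death rule.** Assume identical discharge times (lognormal, median 18 days, log-SD 0.6, capped at 28), mortality of 35% in control and 20% in the trial arm, and deaths spread evenly over days 1 to 14. Counting survival days as stay then makes the trial arm average 1.6 days longer, and the test is significant in 25% of 2,000 runs. The arm with fewer deaths looks worse.

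**The case against.** The strongest reply is that the article nowhere ties hospital days to day 28. That day is attached to mortality and pathogen clearance, and 28 days is the length of treatment. If each patient is followed until death or discharge, the two classes cover everyone and nobody is lost. Adverse events refers to a follow-up period, and most patients enrolled before May 31, 2021 could be observed well beyond 28 days. This stands as a condition on the finding. It does not remove it: no follow-up to discharge is described, and a patient entering on May 31, 2021 has only about 30 days before the study closes.

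A reader might also infer that hospital days and ventilation time are whole-stay durations that necessarily include time before randomisation. The text does not support that. It states no origin for either outcome. Counting from admission is a natural reading of hospitalization days, while survival days in a trial usually run from entry. Ventilation time is only named. A condensed article may leave such detail to the full protocol, so an unstated origin is a point to clarify rather than an error.

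Nor should the result be put as 8 days falling to 0.9, since a scale capped at 28 days would itself show only 2.6.

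**Conclusion.** The stated definition of hospital days leaves survivors who are still in hospital without a value. If observation ends at day 28, the longest stays are removed according to a post-randomisation outcome, and a true difference is attenuated: from 2.6 to 0.9 days under the exponential assumption and from 3.3 to 1.4 days under the gamma. In the simulations, power fell from 83–86% to 34–71%. All of these sizes rest on assumed stay distributions without deaths, and they shrink if patients are in fact followed to discharge.

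The unstated time origin is a lesser matter. If the count starts at admission, the 72 h or more before entry costs precision and causes no bias. For ventilation time, no more can be said than that its window is undefined. These are secondary outcomes, and the primary conclusion is unchanged.

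**What to change.** Under Secondary outcomes, replace the definition with one that gives every randomised patient a value:
- Count hospital days from randomisation to day 28.
- Give survivors still in hospital at day 28 the full 28 days.
- State a death rule on the same scale so that an early death is not a short stay. One option is hospital-free days to day 28 (28 minus hospital days for survivors), with zero for patients who die by day 28.
- If ventilation time is compared, use the same window.
- Report hospital stay before randomisation as a baseline characteristic.

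The cost is a few sentences of definition. The day-28 mortality comparison already requires vital status at that day, and hospital days cannot be computed at all without discharge dates; these would be needed for withdrawn patients too. There are two downsides. Stay beyond day 28 is not described. And under the hospital-free scale, deaths and patients still in hospital share the value zero, so it should be read beside day-28 mortality. No treatment or clinical rule changes.

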### Statistical analysis

#### Data analysis

The Longhua Hospital Shanghai University of Traditional Chinese Medicine will be in charge of data management and statistical analysis in this study. Statistical analysts are not involved in clinical observation; they are responsible for statistical analysis of study data and timely delivery of statistical reports to the study director. Statistical analysis will be performed with SPSS 20.0 software. Measurement data are expressed as mean ± standard deviation. Normality test and homogeneity test of variance will be performed first. In case of normal distribution and homogeneity of variance, a *t*-test is performed, otherwise a non-parametric test is used. Count data are expressed as frequency constituent ratio (percentage) and *X*^*2*^ test is performed. *P* < 0.05 indicates statistical significance.

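### The hospitalization-days outcome counts days to death as days of stay, so an arm with more early deaths can appear to have the shorter stay

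*Protocol article*

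**What the plan says.** The last item under Secondary outcomes in the protocol article defines the number of hospitalization days as "survival days of patients who die and hospitalization days of those who survive and are discharged". The rule for deaths is therefore written down: a patient who dies contributes the days survived.

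Other relevant text:

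- Mortality is a separate secondary outcome: "mortality is compared on day 28 between the groups" (Secondary outcomes).
- On the time frame, "The treatment course is 28 days" (Interventions).
- The only rule on early deaths excludes "patients who have been hospitalized less than 72 h or who die within 72 h of hospitalization" (Exclusion criteria). Later deaths enter the outcome.
- Measurement data get a t-test if normality and equal variance hold; "otherwise a non-parametric test is used" (Data analysis). The threshold is P "< 0.05 indicates statistical significance", with no sidedness given.

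No text ranks death as the worst result, treats it as a competing event, or limits the comparison to survivors.

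**The concern.** Length of stay is normally read as a measure of recovery, with fewer days being better. Under this definition, a death in the second week scores as a shorter stay than a discharge in good health in the fourth week. Reversing the direction does not help, because a long stay would then count in favour of patients discharged late. No single direction makes the number interpretable when mortality differs between arms.

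The setting makes this more than theoretical. Patients come from emergency departments and ICUs with multidrug-resistant hospital-acquired pneumonia, and the plan itself expects deaths, since it compares mortality. At stake is the sign of the result: a harmful treatment could be reported as shortening stay, and a life-saving one as prolonging it.

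**Working it through.** **The plan's own figure.** The only derived number nearby is the analysable sample: 100 × (1 − 0.15) = 85 per arm (Sample size). It reproduces. The concern does not depend on it, but it sets the range of 85 to 100 per arm used here.

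**Direction.** Let p be mortality, S the mean stay of patients discharged alive, and D the mean day of death. The outcome as defined has mean

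E[days] = (1 − p)·S + p·D.

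If S and D are the same in both arms, the trial-minus-control difference is

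−(p_trial − p_control)·(S − D).

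Whenever deaths fall on average before discharges (D < S), the arm with more deaths has the shorter mean, although nobody recovered sooner.

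**Inputs.** The article gives no mortality, timing of death or length of stay, so these are assumptions. Discharges are uniform on days 12 to 35, so S = (12 + 35)/2 = 23.5. Deaths are uniform either on days 1 to 14 (D = 7.5) or on days 4 to 28 (D = 16).

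**Mean differences (trial minus control).**

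| Mortality, trial vs control | Deaths on days 1–14 (S − D = 16) | Deaths on days 4–28 (S − D = 7.5) |
|---|---|---|
| 40% vs 25% | −0.15 × 16 = −2.4 days | −0.15 × 7.5 ≈ −1.1 days |
| 30% vs 25% | −0.05 × 16 = −0.8 days | −0.05 × 7.5 ≈ −0.4 days |
| 20% vs 40% | +0.20 × 16 = +3.2 days | +0.20 × 7.5 = +1.5 days |

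**How often this is significant.** Simulated trials used the Mann-Whitney test at two-sided 0.05 (two-sided is assumed) and 85 to 100 per arm:

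- 40% vs 25%: the harmful arm is significantly shorter in about 37 to 42% of trials with deaths on days 1 to 14, and in about 13 to 15% with deaths on days 4 to 28.
- 30% vs 25%: about 4 to 8%.
- Equal mortality: about 2.5% in each direction, so there is no bias.
- 20% vs 40%, 100 per arm, deaths on days 1 to 14: the life-saving arm is significantly longer in about 67% of trials.

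The t-test behaves almost identically (about 42% in the first case at 100 per arm), so the choice of test under Data analysis does not matter.

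**Same data with death ranked worst.** Using hospital-free days to day 28, the harmful arm is significantly favoured in under 1% of trials across these scenarios. In the 20% vs 40% case at 100 per arm, the life-saving arm is correctly favoured in about 70%.

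**A check under other assumptions.** Take 85 per arm, a mean stay of 24 days with SD 8 for survivors, and exponential death times with mean 8 days plus 1, capped at day 28. The arm with more deaths is then significantly shorter in 14% of runs at 30% vs 20% mortality, and in 47% at 40% vs 20%.

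**The case against.** **It is a minor outcome.** It is the last-listed secondary outcome. Neither the primary outcome nor the sample size uses it, and the Discussion does not list it among the measures expected to confirm efficacy. This stands and limits the severity to moderate.

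**Mortality is compared separately.** Excess deaths are not hidden. At 100 per arm, a chi-square test on mortality alone is significant in about 63% of trials at 40% vs 25%, and in 89% at 20% vs 40%. The second figure exceeds the power of hospital-free days, much of which comes from mortality anyway. This also stands, but a mortality result beside the outcome does not correct the outcome's own estimate or P value.

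**Direction and pooling are inferred.** The article does not say that fewer days is favourable, or that the two day counts form one mean. It does put both under one named outcome without providing for separate reporting. If they were reported separately, each would be conditional on an event after randomisation.

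**The size rests on death timing.** This is correct. Early deaths that barely overlap with discharges give the largest effect, so only a range is defensible. A death on day 3 is also a poor example: if days run from admission, the 72-hour exclusion removes that patient. Starting deaths on day 4 and ending on day 14 still gives a rate close to 40%, so the mechanism does not depend on such cases.

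**Ventilation time.** A reader might infer the same flaw there. The article says only "Comparison of mechanical ventilation time and success rate of weaning off the ventilator are calculated if appropriate" and states no rule for deaths. Handling of death for that measure may sit in the full protocol or analysis plan, which is not at hand, so the inference is not supported.

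**Conclusion.** The point holds for the number of hospitalization days, as an error in a stated rule rather than an omission. Followed as written, the outcome can point the wrong way when mortality differs between arms and deaths tend to precede discharges.

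Under the assumed 40% vs 25% mortality, the false shortening is about 1.1 to 2.4 days and reaches significance in about 13 to 42% of trials, depending mainly on when deaths occur. With a 5-point excess it is about 4 to 8%, and with equal mortality the bias vanishes. Every rate and day count here is an assumption.

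A reader might go further and infer that the trial's main conclusion is compromised or that harm would go unseen. The article does not support that: the primary outcome is unaffected and day-28 mortality has its own comparison. Severity is moderate.

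**What to change.** Redefine the outcome as hospital-free days to day 28 in all randomised patients. Rank death as the worst value, give zero free days to patients alive but still in hospital at day 28, and compare arms with a rank test. This also gives a value to patients who have neither died nor been discharged. Alternatively, analyse time to discharge alive with death as a competing event. In either case, show the already planned day-28 mortality comparison directly beside it.

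The cost is a change of definition. It needs only the death and discharge dates that the present definition already requires. The small downside is that hospital-free days partly reflect mortality, which is why the two results should be read together.

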### Data collection and management

Data will be managed using the electronic data capture (EDC) system. The study protocol and case report form (CRF)-related materials are provided by the research team to a professional institution for clinical data management and study data statistics, which will establish an electronic case report form (eCRF) for the team, set up a personalized database for data recording, and is responsible for management of the study site’s EDC system. The Standard Protocol Items: Recommendations for Interventional Trials (SPIRIT) flowchart of the trial is shown in Fig. 2.

**Fig. 2 Fig2:**
[figure not shown]
Standard Protocol Items: Recommendations for Interventional Trials (SPIRIT) flowchart

### Data monitoring

During the study, an independent data monitoring committee (DMC) will be set up to carry out periodic interim evaluation and optimize the study when appropriate based on the results of the interim evaluation. The DMC is authorized to discontinue the clinical study in case of unexpected adverse reactions. During implementation of the project, the original trial data will be subject to audit and random inspection periodically or irregularly and study compliance will be checked, so that data integrity and accuracy will be fully guaranteed and authenticity and reliability of the study results are ensured.

### Adverse events

Any untoward medical event that occurs in subjects during observation of a clinical study, whether or not it is causally related to the investigational drug, is considered an adverse event (AE). The AE report form is to be completed during the trial. The time of occurrence, severity, duration, actions taken, and outcomes of AEs are recorded. AEs occurring during follow-up should be reported in a timely manner to the sponsor; in case of serious AEs, the events should be reported to the adverse drug reactions (ADR) monitoring center of the local authority within 24 h, and to the sponsor at the same time.

### Sample size

Considering that no previous studies have been conducted to calculate the sample size, and assuming that the withdrawal rate is less than 15% [23], we expect that 100 patients will be enrolled in each arm, and that the final sample size of each arm will be at least 85. The data we collect will be helpful to calculate the appropriate sample size in the future and provide reference for further large-scale research.

